**Project Name: Using Technology to Improve Eating Disorders Treatment**

**Principal Investigators (PIs): [name] Ph.D. & C. [name].**

### **1. Background/Rationale/Literature**

Despite the pressing need for intervention, current treatment delivery standards for eating disorders (EDs) on college campuses are hindered by minimal screening efforts, limited access to evidence based care, and exceeded capacity for intervention. College campuses are faced with an elevated prevalence of EDs as the risk for onset is highest in late adolescence and early adulthood. Rates of EDs are estimated as high as 13.5% and 3.6% for US college age women and men, respectively. However, less than 20% of students who screen positive for EDs report receiving treatment. Delays in treatment delivery result in prolonged illness, disease progression, poorer prognosis, and greater likelihood of relapse. Reported barriers to service utilization on college campuses include unawareness of services, skepticism of treatment effectiveness, and lack of perceived need. Online screening and intervention offers an ideal medium through which to increase access to care, improve outcomes, reduce costs, and establish a self-sustaining system for providing mental health services. Online interventions have been successfully used for treatment and prevention of EDs, with high user acceptability given their accessible and anonymous format. However, an online platform through which screening and tailored interventions are provided to individuals with various levels of risk or ED diagnosis has not been deployed. Our research team has successfully developed a comprehensive, internet-based platform through which we identify and offer tailored evidence-based interventions to individuals across the ED risk and diagnostic spectrum using minimal person based resources. The newest intervention in our suite of programs has not yet been tested in a large scale trial or via platform delivery. The aim of this study is to conduct the first national deployment of our comprehensive platform and demonstrate that our transdiagnostic guided self-help program, Student Bodies-Eating Disorders (SB-ED), improves access, costs, and outcomes of mental health care for EDs.

### **2. Hypothesis/Key Questions**

We believe our platform will demonstrate a significant impact on access, costs, and outcomes for the treatment of EDs. Integrated screening and intervention will result in increased access (i.e., receipt of ED treatment) to mental health care by identifying students with an ED, automatically directing them to easily accessible care, and tracking their progress over time. Comparison of implementation and service costs between SB-ED and usual care has the potential to demonstrate improved costs (i.e., positive net benefit from a health care payor's perspective) for the treatment of EDs. Our previous small scale efficacy testing suggests that SB-ED will be associated with improved outcomes (i.e., decrease in ED pathology and functional impairment) over referral to usual care.

### **3. Research Objectives and Purpose**

Our research goal is to demonstrate that delivery of SB-ED via our online platform significantly improves the system of care for EDs on college campuses. The goal of SB-ED is to target the core pathology of ED diagnosis and to provide tailored content to address specific ED features based on individuals' symptom profile. Though our target conditions are classified as categorical diagnoses, the shared latent pathology of EDs across the binge/purge spectrum makes a comprehensive, diagnostic approach ideal for treatment. Our approach is comparable to the transdiagnostic model that has been applied to the treatment of EDs, which addresses pathology common across ED diagnoses but incorporates tailored intervention components specific to the presenting symptoms. Our interventions include mobile technology that allows users to provide ongoing, real-time assessment of symptom progression. We also use clinical data management "dashboards," sophisticated online tools that allow moderators to visually represent individual users' progress over the course of the intervention to efficiently monitor multiple users at one time. These tools set the stage for scale up by increasing relevance and efficiency.

### **4. Research Methods**

Our approach will use an evidence based stepped care framework. Given that the need for treatment outweighs clinician capacity, guided self-help interventions are recommended as a first line treatment,

with standard in person treatment offered in the event of worsening or maintenance of symptoms. Flexible online modalities allow us to expand this paradigm by tailoring interventions over the course of treatment, making the intervention more interactive than guided self-help books and, by offering interventions via computer and phone, more congruent with students' routines. Consistent with the guided self-help model, moderators will coach and motivate students through the program. The program itself will include twenty eight colleges, each of which will be allocated at random to receive either SB-ED or referral to usual care (i.e., treatment per protocol at students' corresponding college's mental health services center). Campus selection criteria are based on interest and population size. We will recruit 28 schools across the United States. We will require that colleges identify a clinical liaison in the student mental health services center. We will seek IRB approval or acknowledgment at all participating schools and obtain informed consent from student participants. The clinical liaisons will partner with moderators at study sites to deploy the intervention, field clinical referrals, and communicate with study staff regarding any adverse events. The clinical liaison will also update the PIs regarding campus staff and students' impressions of the initiative. As another incentive, schools will receive the evidence based Student Bodies-Targeted and StayingFit programs to offer students who do not have an ED, regardless of study condition. This will complement the screening efforts and afford schools a comprehensive solution to improve the health and well-being of their students. Students will complete an online screen and then be triaged to appropriate care based on their presenting symptoms: Student Bodies Eating Disorders, Student Bodies Targeted, Staying Fit, or a clinical referral. We will enroll at least 650 students who screen positive for a DSM 5 clinical or subclinical ED, defined as DSM 5 bulimia nervosa (BN), binge eating disorder (BED), subclinical BN (sub BN), subclinical BED (sub BED), or purging disorder (PD). Individuals who screen positive for DSM 5 anorexia nervosa (AN) will be offered a referral, given that the medical severity of AN warrants more intensive clinical intervention. All participants will take the online screen which assesses demographics (sex, race/ethnicity, age), ED related attitudes and behaviors, and clinical impairment. Self-reported height and weight will also be collected to calculate BMI. Participant outcomes will be assessed with the Eating Disorder Examination Questionnaire (EDE-Q) version 6, a 39 item measure of eating pathology and symptom severity. The Weight Concerns Scale (WCS) is a reliable and valid measure of eating attitudes and predicts ED risk. Measures of comorbidities include the Patient Health Questionnaire (PHQ-9), a measure of depression symptom severity; the Patient-Reported Outcomes Measurement Information System (PROMIS) anxiety short-form v. 1.0-Anxiety4a questionnaire, a measure of anxiety severity; and a measure of alcohol use. Measures of impairment include the Clinical Impairment Assessment (CIA), a 16-item measure of clinical impairment due to ED-related problems; and the College Student Eating Disorder Related Academic Impairment Scale (CS-ED AIS), an 8-item self-report measure created by the research team to measure ED related impairment across academic domains. Additionally, we will capture continuous measures of symptoms across a range of mental health problems relevant to college students via administration of the Counseling Center Assessment of Psychological Symptoms 34 (CCAPS-34). The CCAPS-34 is a 34 item scale condensed from the CCAPS-62 and can be completed on average in 2-3 minutes. We are partnering with a software platform (Lantern) to provide online, evidence based interventions to defined populations. Specifically, our platform includes StayingFit (for low-risk students), Student Bodies-Targeted (for high-risk students) and the program that will be examined in this study, SB ED. All programs are derived from evidence based, cognitive behavioral interventions. (Note, in the current study, the only intervention under evaluation will be SB-ED.) The platform is structured so that programs can be revised and enhanced depending on outcome and can address multiple mental health issues. SB-ED is the latest program in a set of programs we have developed. The intervention is a structured, cognitive behavioral program, derived from manual-based cognitive behavioral therapy. The intervention targets the core ED pathology (e.g., extreme dietary restraint, overvaluation of shape and weight, binge eating, compensatory behaviors), focusing on helping users develop regular eating patterns, self-control strategies, problem solving skills, and relapse prevention tools for maintenance of behavior change. SB-ED also provides tailored content to address specific ED features based on individuals' symptom profile. We include content related to coping with negative emotions including skills training and inclusion of elements from dialectic behavior therapy (e.g., acceptance of negative emotions, mindfulness, and mindful eating), as well as psychoeducational content on social skills and cognitive restructuring. The program includes symptom checklists (assessing weight, number of meals per day, and number of binges and compensatory behaviors per day), journal exercises and activities, and a discussion group (through which users can interact anonymously to discuss reactions to the program, seek advice, or ask questions to peers or the moderator). Program moderators will be clinical psychologists or advanced graduate student

trainees under the supervision of a clinical psychologist or psychiatrist. Campus clinical liaisons may also moderate the program after receiving training. Moderators will guide and motivate students in using the program, check daily to monitor participant progress and provide individualized feedback, and moderate the discussion group. Senior personnel will provide additional oversight by reviewing weekly behavior logs and discussion group postings. SB-ED includes exciting, new technological features to make the platform more attractive and efficient, to increase engagement and monitor individuals' progress in real time.

#### 4.1 Amendments to the Research Methods

The initial plan was to enroll and recruit from 28 U.S. universities. The study team enrolled and randomized 30 universities, however 3 dropped out before recruitment at those sites began. As such, 27 universities participated in the data collection. (Approved by IRB on 4/02/14)

The program also started with the use of a discussion board, to allow users to interact with one another. However, as the program platform changed, the discussion board functionality was removed. A separate discussion board was created outside of the platform for users to engage with if they wished. To supplement this interaction with moderators, users of the SB-ED program were assigned a coach, who was a clinical psychologist or advanced graduate student trainees under the supervision of a clinical psychologist or psychiatrist. Coaches could message back and forth through a secure system with the users, and help them understand the program content and apply it to their own situations. The coaches also helped to increase engagement by reaching out to the users and reminding them about their next session. (Approved by IRB on 07/06/2015).

The SB-ED program was changed to improve engagement from an 9 unit weekly program to a 40 session daily program. The content from the nine sessions was primarily the same, but spread out across more, shorter, sessions. (Approved by IRB on 07/06/2015).

#### 5. Study Participants

We will use recruitment methods based on our previous trials. Potential participants will be recruited from flyers posted at local academic institutions, campus mailings and emails, and mass media. Schools may also elect to deliver the screen in a population based format to all or a defined subset of students (e.g., mandated screens; including the screen with new student orientation materials; offering it at routine medical visits). Members from the research team will assist colleges to advertise the screen and/or assist school administrators in implementation of a population based delivery.

Participant recruitment will occur in three waves, of three consecutive academic calendar years. We will terminate recruitment from February through the end of the academic year, as students requiring clinical referral will not have adequate time to pursue a standard treatment regimen (12 weekly sessions) at the mental health services center before the end of the semester. Entry into discussion groups will be rolling, as in group psychotherapy in clinical settings. Given that all assessments will be completed online, follow up will occur throughout the year, regardless of schools' schedules. Online gift cards will be used to incentivize participants to complete follow-up assessments.

Given that rates of EDs in males are much lower than in females, our study enrollment goals will be limited to females; however, males with EDs will be welcome to participate. The interventions will be provided to males in sex specific groups. Data collected from men will be exploratory.

Participants will include students, ages 18 to 30, at the participating colleges and universities who screen positive for a DSM 5 clinical or subclinical ED (excluding AN). We intend to enroll 650 students into the trial, equivalent to 25 students per site. Eligible participants will not be currently undergoing treatment for an ED, have access to the internet, and not be acutely suicidal.

Interested individuals at all of the schools, regardless of the randomization condition, will be eligible to complete the online screen. The screen takes less than 5 minutes to complete and can be administered online via computer or Smartphone. Students immediately receive screen results in an email, indicating whether an intervention or clinical referral is recommended based on their presenting risk or symptom status. Individuals screening positive for a clinical or subclinical ED (excluding AN) will be invited to

participate in the trial. A study description will be provided in the email with screen results. Following the study description, consent will be obtained in a secure online format as well. For those prompted to an intervention, a link to the program, program description, a randomly generated username, and a randomly generated password are also included in this email. Students are encouraged to log in to the intervention, change their username and password to an anonymous one of their preference, and begin the program. Students who warrant a clinical referral (either because they are in the control condition or because they screen positive for AN) will receive an immediate email as well indicating this recommendation, with contact information for the student mental health services center. All students will receive an automatic email prompt one week following screen completion, reminding them of their screen feedback and encouraging them to pursue the recommended strategy. Preferences for additional follow up procedures can be specified by the schools on a campus by campus basis.

## 5.1 Study Participant Amendments

Additional recruitment methods were used besides the ones originally detailed. For example, the study team conducted tabling events on campuses to screen students, as well as presentations in classes at student group meetings. (Approved by IRB on 02/19/15)

Participant recruitment was originally delayed to January of 2014, due to a delayed launch of the program on campuses. It was determined that campus mental health services would connect students with therapeutic options to bridge the summer if the students received a referral close to the end of their spring semesters. As such, recruitment was continuous from the start of January 2014 until July of 2016. (No IRB approval given for this change, as recruitment was approved for anytime following initial approval on 09/05/13).

Regarding eligibility criteria, participants were allowed to enroll as long as they were 18 years old or over, and students at the university participating in the study. It was decided that participants could also be receiving in-person treatment (an original exclusion criteria), because referral to in-person care was offered to those who did not progress by mid-program. (Approved by IRB on 05/19/14)

The screen result was still immediate, but did not arrive via email (as previously described). The screen result was presented at the end of their survey. For the participants in the referral condition, they immediately received contact information for their campuses resources. For those that were in the intervention condition, they were given a link to complete their first baseline, should they choose to participate. The participants were able to progress from the screen, to the baseline, to the program login page, and were allowed to create their own username and password to being the program. (Approved by IRB on 11/05/14)

The outcome of interest is the net benefit of treatment, comparing SB-ED to referral to usual care at 24 months. We define net benefit as the difference between cost of providing care (from the payor perspective) and cost of SB-ED. Secondary Aim 5. For our primary outcome, EDE Q total scores, we will examine baseline variables (e.g., site and patient characteristics, patient comfort with and acceptance of technology based intervention) as potential moderators. Potential mediators of subsequent outcomes include baseline to 6 month reduction in weight and shape concerns and dietary restraint. Similar potential mediators and moderators will be explored for our secondary outcome pertaining to abstinence rates. For our secondary outcome pertaining to treatment access, potential moderators consist of variables such as patient characteristics and site characteristics. In addition to the above, we will examine within group SB-ED group correlations between treatment adherence variables (e.g. completion of self-monitoring forms) and changes in EDE-Q total scores.

## 7. Potential Problems

### Risks to the Participants

There are no high risk or hazardous aspects of our proposed intervention. One potential risk includes accidental disclosure of private, identifiable information. The information will be housed on a HIPAA protected server and will only be downloaded from the server after being de-identified. We recognize that a program to provide guided self-help for eating disorders may promote increased focus on body image and eating attitudes and behaviors, more than that which may exist before starting the program. Due to increased sensitivity, the participants in the program will be monitored by trained moderators, supervised by licensed psychologists, at Stanford University, Washington University, or the participating study sites. Given our use of a stepped care approach, additional risks may present themselves. This study involves individuals who are screening positive for eating disorders; individuals in the intervention condition are being offered an online moderated guided self-help intervention. However, referral to in person treatment will be recommended to users in the event of worsening symptoms. It is possible that without intensive care, participants' symptoms could remain stagnant or increase over the course of the intervention. If any participant appears to be in crisis or exhibiting symptom worsening, appropriate action will be taken based on established suicide and crisis assessment protocol.

### Minimization of Risk

The overall risks for this study are minimal. Participants' diagnostic information, obtained from the screen, will be kept private to minimize potential embarrassment related to diagnosis. There are minimal risks for participating in the program. Students will be provided with the contact information of their program moderator, study staff, and students' corresponding college's clinical liaison at the mental health services center. All information will be kept on a HIPAA compliant server. Prior to implementation, the server will be audited by a third party to ensure all technical and protocol requirements are met. The technology meets current standards for privacy; subsequent versions of iPhone technology that are released that have the same security protections may be used, as they remain in compliance with the current privacy standards.

Moderators will monitor students' progress via the online intervention clinical data management "dashboard" and online group discussion board. The dashboard is a sophisticated online tool that allows clinicians to visualize individual users' progress to efficiently monitor multiple users at one time. Moderators will be prompted to send email message reminders to participants to complete the logs. To ensure HIPAA compliance, email messages will be standardized messages merely alerting users that they have a message on their program homepage or a reminder to complete their behavior logs online.

The discussion board provides an anonymous arena for multiple users to post comments, offer feedback, and give reactions to the program content. As such, this may give participants a space to post demeaning or inappropriate comments to other participants. We have a zero tolerance policy for such postings and we will caution against them in three ways: (1) participating students can flag negative posts (four flags will result in removal from the program); (2) moderators will conduct random, daily site checks; and (3) the network will track negative key words and alert study staff to intervene through the clinical dashboard. As an extra precaution, we will address these issues in the subjects' online "netiquette" (i.e., internet etiquette) training prior to starting the program. It is worthwhile to note that we have used these practices successfully in studies involving over 1000 students participating in over 30 online groups, and we have never received complaints or had adverse events as a result of the online program or discussion board.

Each week, the progress, process, and postings in the electronic discussion group and behavior logs will be reviewed by a psychologist or psychiatrist through the Dashboard. If students do not achieve 50% symptom reduction by session 6 of the intervention or symptom abstinence following the intervention, they will be offered an on campus referral. At the 6-month assessment, students who remain in the sub-clinical or clinical eating disorder range will be referred to the student mental health service center.

The senior behavioral scientist will train program moderators, including how to address safety issues. Materials will also be provided to the college's clinical liaison at the mental health services center regarding safety issues. In addition, the clinical dashboard and discussion board will be accessed by the study moderator at least once daily. Discussion board postings will be monitored for signs of dangerous changes in weight related behaviors (i.e., bingeing, purging, or dietary restriction), severe depression, possible suicide/self-injury, or harm to others. Students who do not report 50% or greater symptom reduction by session 6 of the intervention or symptom abstinence following the intervention will be offered an on campus referral. If any participant appears to be in crisis, appropriate action will be taken based on established suicide and crisis assessment protocol (see below). Any adverse event will be reported promptly to NIMH and to the IRBs at the participating institutions within 72 hours by email.

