### **Potential Risk Amendment**

As noted in the procedures section, a coach messaging system replaced the primary function of the discussion board. As such, the same detailed protocol for ensuring the safety of the participants on the discussion board was applied to the coach messages.

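### The session-6 referral check was not updated when SB-ED went from 9 weekly units to 40 daily sessions, so it now falls at 15% instead of 67% of the program

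*Protocol*

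**What the plan says.** Section 7 of the Protocol (Minimization of Risk) states the step-up rule twice, each time as the condition for an offer of on-campus referral. First: "If students do not achieve 50% symptom reduction by session 6 of the intervention or symptom abstinence following the intervention". Then, with the same session number: "Students who do not report 50% or greater symptom reduction by session 6 of the intervention or symptom abstinence following the intervention".

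Section 4.1 (Amendments to the Research Methods, IRB approval 07/06/2015) changes the program those session numbers refer to: "The SB-ED program was changed to improve engagement from an 9 unit weekly program to a 40 session daily program". It adds: "The content from the nine sessions was primarily the same, but spread out across more, shorter, sessions". The old weekly units are thus also called sessions.

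Section 5.1 (approved 05/19/14) explains why students already in in-person treatment could enrol: "because referral to in-person care was offered to those who did not progress by mid-program".

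Section 7 has its own amendments, under Potential Risk and Protection Against Risk. They deal only with the move from the discussion board to coaching: "the same detailed protocol for ensuring the safety of the participants on the discussion board was applied to the coach messages". Neither mentions session 6.

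**The concern.** Session 6 has a different meaning in the two formats. In the weekly program it comes after most of the content. In the daily program it comes near the start, yet the student must still have halved their symptoms to avoid the offer.

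Section 4 describes stepped care: guided self-help first, in-person care if symptoms get worse or do not change. A 50% threshold applied very early does not pick out those students. It also catches students who are improving at a reasonable rate but have had little time or content. It also conflicts with the mid-program timing that section 5.1 relies on for an eligibility change.

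What is at stake is the description of the strategy under test. Referral to campus services is what defines the control arm (section 4). A reader cannot tell whether daily-format SB-ED students were to be offered it in about their first week or around the middle of the program. Secondary Aim 1 (ED treatment received between baseline and 6 months) and Secondary Aim 4 (cost of care against cost of SB-ED) are the results most directly tied to that.

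**Working it through.** The Protocol gives no percentage for the position of the check, so there is no stated figure to reproduce.

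**Inputs.** Check at session 6 with a 50% reduction (section 7); 9 weekly units, then 40 daily sessions with mainly the same content (section 4.1); check described as mid-program (section 5.1).

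**Position of the check** = session number / total sessions.
- Weekly format: 6/9 = 66.7%, about week 6.
- Daily format: 6/40 = 15.0%, about day 6 if one session is done each day.
- Content covered by session 6 of 40, in original units: 9 × 6/40 = 1.35.

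**Equivalent points in the daily format.**
- Same share of content as unit 6 of 9: 40 × 6/9 = 26.7, so about session 27.
- Midpoint: 40 × 0.5 = session 20. The midpoint of the weekly program is 9 × 0.5 = 4.5 units, so unit 6 was already only loosely mid-program. Session 6 of 40 is not mid-program on any reading.

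**Who would be flagged: an illustration on assumed paths.** Suppose the reduction depends on the fraction *f* of the program completed. A linear path ending at reduction *R* gives *R* × *f*. A front-loaded exponential path ending at *R* gives 1 − (1 − *R*)^*f*. The student passes at 50% or more.

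| Assumed path | Session 6 of 9 (f = 0.667) | Session 6 of 40 (f = 0.15) | Session 20 of 40 (f = 0.50) |
|---|---|---|---|
| Linear, R = 100% | 66.7% | 15.0% | 50.0% |
| Linear, R = 90% | 60.0% | 13.5% | 45.0% |
| Exponential, R = 90% | 78.5% | 29.2% | 68.4% |
| Exponential, R = 99% | 95.4% | 49.9% | 90.0% |

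All four students pass at session 6 of 9 and all four fail at session 6 of 40. The last one fails only just: solving 1 − (1 − R)^0.15 = 0.5 gives R of about 99.02%, above which the student passes. At session 20 the linear 90% path still fails. At the content-matched point (f = 0.667) every row returns to its weekly-format value.

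**How much of recruitment is involved.** Section 5.1 says "recruitment was continuous from the start of January 2014 until July of 2016". If the daily format began on its approval date (an assumption), the days from 6 July 2015 to 1 July 2016 are 361 of 912, or 39.6%. Counting to 31 July 2016 gives 391 of 942, or 41.5%. This is calendar time; the Protocol does not give the share of students.

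**The case against.** The best defence is that this is a leftover phrase. The Protocol keeps its original text and appends amendments. Section 7 still treats the discussion board as a live tool after section 4.1 removed it from the platform, and section 4.1 calls the old units sessions. A reader could take session 6 to mean the content of old unit 6. Section 5.1 reports in the past tense that the offer was made around mid-program, and that wording was approved while the program still had nine units. This defence stands in part: it shows how the mismatch arose. It does not remove it, because section 7 received its own amendments and the threshold still names a session number that now points elsewhere.

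Four stronger readings are tempting, and the document does not support them.

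- *That daily-format students were in fact checked at about day 6.* Nothing shows this. Day 6 also assumes one session every day, and section 4.1 has coaches reminding users about their next session.
- *That safety monitoring failed.* The referral for worsening symptoms is separate, and so is the clinician review: "Each week, the progress, process, and postings in the electronic discussion group and behavior logs will be reviewed by a psychologist or psychiatrist". The abstinence check after the program and the referral at the 6-month assessment do not depend on session 6. The 6-month referral also covers students who never reach session 6, a gap that existed in the weekly format too.
- *That the wait until the next program-based check became many times longer.* Counting remaining sessions mixes units. At nominal pace, 34 daily sessions are 34/7 = 4.9 weeks, against 3 weeks for the last three weekly units.
- *That the comparison of arms is contaminated.* Stepped care is the stated design, referral offers in the SB-ED arm were always planned, and concurrent in-person treatment was allowed. An offer is also not treatment received.

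**Conclusion.** The point holds as an uncorrected rule in the current text. The mid-course referral check moved from 67% to 15% of the program through a change of format, and no section redefines it. As written, it disagrees with the mid-program timing in section 5.1 and with the step-up criterion in section 4.

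The positions follow directly from the Protocol's own numbers. The statement that most daily-format students, including improving ones, would meet the referral condition rests on the assumption that improvement roughly follows the share of the program completed. A student whose symptoms fall very steeply at the start could still pass.

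Which check was applied in practice is unknown. Any effect on Secondary Aims 1 and 4 cannot be sized from the Protocol, and no effect on the primary EDE-Q comparison is claimed. The correction is worth making because the rule sets who is offered the next step of care, and it is cheap to put right.

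**What to change.** In both statements of the rule in section 7, replace the session-6 condition with: by unit 6 of the 9-unit program, or the matching point of the 40-session program. Then name that point. Session 27 keeps the original share of content; session 20 is right if mid-program is what was intended. The choice is clinical, and the table shows that it matters for students who improve steadily but incompletely. Leave the worsening trigger, the weekly review, the end-of-program abstinence check and the 6-month referral as they are.

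Because recruitment has ended, also state which check daily-format students actually received. If the dashboard and coach records allow, report the number of referral offers in the SB-ED arm by program format, next to the results for Secondary Aims 1 and 4. If they do not, state this as a limitation.

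The cost is one phrase changed in two places and a tabulation from existing records. No new data collection is needed.
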